#### STIckER

The adolescent and young adult participants, randomized to the intervention, will complete the STIckER web-based app, which includes a 13-question sexual health assessment. This includes a validated 6-question survey of age and STI-related behaviors, as well as locally developed questions about types of sexual activity engaged in the previous 3 months, and if they had received gonorrhea or chlamydia testing in the previous 30 days [26,27].

#### Exit Survey

Immediately after a visit with an HCP-P, the adolescent and young adult participants will complete an exit survey.

The adolescent and young adult participants randomized to the control arm will complete questions on whether STI testing was discussed (“Did you and your patient discuss STI testing”), if the discussion was appropriate (Likert scale of 1‐5, from “completely appropriate” to “completely inappropriate”), if STI testing was ordered, and if STI testing was ordered, then what level of shared decision-making involvement occurred using the control preferences scale. The Control Preferences Scale is used to assess the extent to which patients perceived that the decision about STI testing was shared between themselves and their provider. It captures patient-reported involvement in the decision-making process by asking who took the lead in making the decision. While it does not measure specific components, such as depth of discussion or mutual agreement, it is a validated and widely used measure of perceived shared decision-making.

They will also complete 4 questions on the amount of information received, clarity of information received, helpfulness of information received, and if they would recommend that information to others; 9 items from the decisional-conflict scale on uncertainty. They will complete 2 items, providing a rating of the ED (0 to 10) and if they would recommend the ED to family or friends. Finally, they will complete the 13-question sexual health assessment that was included in STIckER.

The adolescent and young adult participants randomized to the intervention will complete questions on whether STI testing was discussed (“Did you and your patient discuss STI testing”), if the discussion was appropriate (Likert scale of 1‐5, from “completely appropriate” to “completely inappropriate”), if STI testing was ordered, and if STI testing was ordered, then what level of shared decision-making involvement occurred using the control preferences scale. They will also complete 4 questions on the amount of information received, clarity of information received, helpfulness of information received, and if they would recommend that information to others; 9 items from the decisional-conflict scale on uncertainty [28]. They will complete 2 items, providing a rating of the ED (0 to 10) and if they would recommend the ED to family or friends. Finally, they will complete the AIM, IAM, and FIM implementation measures.

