#### Intervention Participants

Patient participants in the intervention arm will proceed through the following 5 modules (see Figure 1):

STI education**:** STIckER starts with a 1:06-minute video describing the importance of STI testing, followed by additional information about STIs and testing for STIs (see Figure 1).Sexual health assessment: Participants complete a 13-question assessment to assess their vulnerability to STIs. This assessment categorizes participants into high, medium, or low need for testing and generates recommendations for genitourinary, rectal, and oral gonorrhea and chlamydia testing at the time of ED visit (see Figure 1).Decision-making and shared-decision-making modules: Participants are taken through each recommendation with additional education and the option to opt in or opt out of testing (see Figure 1, panel C). Participants who are “intermediate need” for needing testing at that visit are taken to an additional shared decision-making module that accounts for individual values and preferences (see Figure 1).Provider display: STIckER ends with a hidden display uncovered when the provider places their finger over the STIckER logo to reveal it. This reveals testing recommendations and patient choices for oral, rectal, and urinary testing (see Figure 1).

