### Study Assessments

#### HCP-P Study Assessments

At enrollment, enrolled HCP-Ps will complete a basic demographic questionnaire. (age, race, ethnicity, sex at birth, gender identity, years since completing training, and type of clinical training completed).

The exit survey will be conducted immediately after a visit with an adolescent and young adult participant; the HCP-P will complete an exit survey.

HCP-Ps randomized to the control arm get questions on whether STI testing was discussed (“Did you and your patient discuss STI testing”), if the discussion was appropriate (Likert scale of 1‐5, from “completely appropriate” to “completely inappropriate”), if STI testing was ordered, and if STI testing was ordered what level of shared decision-making involvement occurred using the Control Preferences Scale (Likert scale of 1 to 5, from “I made the decision on my own” to “the patient made the decision on their own”) [22].

HCP-Ps randomized to the intervention will get the same questions on whether STI testing was discussed, if the discussion was appropriate, if STI testing was ordered, and if STI testing was ordered, what level of shared decision-making involvement occurred using the control preferences scale. They will also complete validated questions on implementation (acceptability of intervention measure [AIM], intervention appropriate measure [IAM], and feasibility of intervention measure [FIM]) [23].

The postsurvey will be conducted after completing their participation in the STIckER study (a maximum of 6 adolescent and young adult participants or the study completing overall enrollment), HCP-P will complete a postintervention questionnaire.

HCP-Ps, randomized to the control arm, will complete a self-efficacy questionnaire to measure their clinical communication skills [24].

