### Outcomes

#### Primary Outcome

The primary outcome of preliminary efficacy is the difference in the proportion of sexually active adolescents and young adults tested for Neisseria gonorrhoeae or chlamydia trachomatis between the 2 arms based on the EMR review. We selected preliminary efficacy as the primary outcome because the trial was designed and powered to provide an effect size estimate that would inform the design and sample size calculations for a future multisite trial. While many pilot studies emphasize feasibility and acceptability as primary outcomes, in this single-site trial, we aimed to generate robust preliminary data on testing uptake to guide scale-up and ensure generalizability across diverse ED settings.

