#### Secondary Outcomes

Secondary efficacy outcomes include rates of extragenital Neisseria gonorrhoeae or chlamydia trachomatis testing, overall and site-specific STI positivity rate, decisional conflict, and level of shared decision-making. Secondary implementation outcomes include feasibility (FIM), acceptability (AIM), appropriateness (IAM), and personal traits and attitudes toward STI screening.

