## Discussion

### Hypothesis

This protocol outlines an RCT to assess the preliminary efficacy and implementation of the STIckER app, a shared decision-making tool to support gonorrhea and chlamydia testing in adolescents and young adults in EDs. We anticipate that the intervention will lead to a higher proportion of adolescents and young adults receiving comprehensive genitourinary and extragenital STI testing compared to usual care, and that both patients and providers will find the tool acceptable, appropriate, and feasible to implement.

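### The Control Preferences Scale is asked only when STI testing was ordered, so comparing level of shared decision-making between arms uses non-randomised subsets and leaves decisions not to test unscored

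*Protocol article*

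**What the plan says.** Secondary Outcomes in the protocol article names, among the secondary efficacy outcomes, "decisional conflict, and level of shared decision-making". The instrument described for the second of these is the Control Preferences Scale.

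Exit Survey gives the scale to patients in each arm under the same condition: "and if STI testing was ordered, then what level of shared decision-making involvement occurred using the control preferences scale". HCP-P Study Assessments applies it to providers in both arms; the control-arm text reads "if STI testing was ordered what level of shared decision-making involvement occurred using the Control Preferences Scale". The condition thus appears four times, for two respondents in two arms.

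Exit Survey also says what the scale is for. It assesses "the extent to which patients perceived that the decision about STI testing was shared between themselves and their provider", a description not limited to decisions in favour of testing. Intervention Participants says the app takes patients through each recommendation with "the option to opt in or opt out of testing".

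The primary outcome is "the difference in the proportion of sexually active adolescents and young adults tested for Neisseria gonorrhoeae or chlamydia trachomatis between the 2 arms", taken from the electronic record. Under Hypothesis the authors expect that "the intervention will lead to a higher proportion of adolescents and young adults receiving comprehensive genitourinary and extragenital STI testing compared to usual care".

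**The concern.** A randomised comparison needs the outcome to be defined for everyone randomised, or at least for a group fixed before the intervention could act. Here a patient has a score only if a test was reported as ordered, and the app exists to change how often that happens. If it works, the scored patients in the two arms are different kinds of patient. A difference in their scores then mixes any effect on how decisions are made with a change in whose decisions are rated.

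The second loss concerns content. A patient who uses the aid, talks with the provider and declines a test has made the kind of decision the tool supports. That visit gets no score from either respondent, so the provider ratings cannot fill the gap.

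At stake is what the trial may say about shared decision-making, and whether the same branch is carried into the planned multisite trial.

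**Working it through.** **1. The passages together.** Scale asked only after an ordered test (Exit Survey, HCP-P Study Assessments); level of shared decision-making is an efficacy outcome (Secondary Outcomes); testing expected to rise in the intervention arm (Hypothesis); opting out is part of the app (Intervention Participants). It follows that being scored depends on a post-randomisation event with an expected arm difference.

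**2. The plan's own figure.** Power Analysis gives a minimum detectable effect of 0.348 for the primary outcome and nothing for this one. Inputs: 44 providers, 140 patients, ICC 0.01, 50% of variance explained at each level, two-sided 5%, 80% power.

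MDE = (t.975 + t.80) × sqrt[ICC(1−R²)/(0.25·J) + (1−ICC)(1−R²)/(0.25·J·n)], with J = 44, n = 140/44 and 42 df

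= 2.869 × sqrt[0.005/11 + 0.495/35] = 0.347.

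The stated figure reproduces. The present point does not depend on it.

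**3. How many patients would be scored.** The article gives no testing rates. Assume 70 patients per arm, control testing of 20%, 30% or 40%, and the 35% increase in Power Analysis read as absolute (first three rows) or relative (last three). Scored = 70 × rate. Detectable difference = 2.80 × sqrt(1/n_c + 1/n_i), ignoring clustering and covariates.

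| Assumed testing, control vs intervention | Scored, control + intervention | Total | Detectable (SD) |
|---|---|---|---|
| 20% vs 55% | 14 + 38.5 | 52.5 | 0.87 |
| 30% vs 65% | 21 + 45.5 | 66.5 | 0.74 |
| 40% vs 75% | 28 + 52.5 | 80.5 | 0.66 |
| 20% vs 27% | 14 + 18.9 | 32.9 | 0.99 |
| 30% vs 40.5% | 21 + 28.4 | 49.4 | 0.81 |
| 40% vs 54% | 28 + 37.8 | 65.8 | 0.70 |

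If all were asked: 2.80 × sqrt(2/70) = 0.47 SD.

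**4. Can selection alone produce a difference?** Give every patient a standard normal sharing score with the same distribution in both arms, so there is no true effect. Let logit P(ordered) = a + b × score, with a set per arm to match the assumed rates (2,000,000 draws). Intervention minus control mean among those with an order:

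- Rates 35 points apart: −0.16 to −0.17 SD for b = 0.5; −0.28 to −0.32 SD for b = 1.0.
- 30% vs 40.5%: −0.05 SD and −0.10 SD.
- Ordering related to the score in the control arm only: −0.28 to −0.69 SD over the same values of b.

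Because the assumed score is symmetric, reversing the sign of b reverses every sign. The direction rests on an association the article does not report.

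**5. Case mix in proportions.** Assume 20% tested in control and 37% in intervention, with 30% of decisions shared among the 20% tested either way. If 70% are shared among the extra 17%, the intervention figure is (0.20×0.30 + 0.17×0.70)/0.37 = 48% against 30%. If 10% are shared among them, it is (0.20×0.30 + 0.17×0.10)/0.37 = 21% against 30%. The contrast among tested patients moves with who is added to the tested group.

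**The case against.** The strongest reply is that only the data collection is fixed here. Preliminary Efficacy states its intention-to-treat analysis for STI testing, and Secondary Efficacy and Implementation Outcomes speaks of continuous outcomes in general. Neither names the Control Preferences Scale or its denominator, and an analysis plan not shown may label it properly. That stands as to the analysis wording. It does not rescue the outcome: answers never asked for cannot be recovered by analysis, and a conditional sensitivity clause mentioning missing data does not address answers absent by design.

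Several stronger readings are tempting and are not supported:

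- A reader might infer that the subsets are selected by the primary outcome itself. The condition is survey-reported ordering of STI testing; the primary outcome is gonorrhoea or chlamydia testing in the record. It is a close proxy.
- A reader might infer that scored control patients are all people who would be tested in either arm. Since the app can lead patients to opt out, some may be people it would have led to decline.
- A reader might call the 18-point gap in the case-mix example spurious, with nobody's decision process changed. In that example the app did change the decision for the extra 17%, and plausibly how it was made. The arithmetic shows mixing, not a known bias.
- A reader might take this as the trial's main measure of the app's mechanism. No section says so. Whether testing was discussed, four information items and nine decisional-conflict items are asked without this condition, though they measure related rather than identical things.

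**Conclusion.** The concern holds in this form: a between-arm comparison of the Control Preferences Scale is not protected by randomisation, and decisions not to test are never rated, although the stated construct covers them. This follows from the text without any assumed number.

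The size is not known. The counts, detectable differences and selection effects above rest on assumed testing rates, equal arms and assumed associations. They show that the loss of information could be substantial and that bias in either direction is possible; they do not estimate it. For one secondary outcome of a pilot this is a matter of what may be claimed, and it leaves the primary outcome untouched.

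**What to change.** Results says surveys are complete and analyses underway, so the change is to reporting and interpretation:

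1. Report the scale descriptively, as conditional on an ordered test, with the number scored in each arm for patients and for providers, and with no p-value or efficacy claim.
2. Base the randomised comparison of the decision process on measures collected from all patients in both arms: whether STI testing was discussed, and the decisional-conflict items.
3. State as a limitation that decisions not to test were not rated. Strengths and Limitations does not mention it.
4. Remove the branch in the multisite instrument, so that every patient and provider rates the decision whatever it was.

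Do not substitute an all-patient composite that counts no test as not shared. It scores a shared decision to decline as a failure and largely follows the primary outcome. In the second case-mix example it rises from 0.20×0.30 = 6.0% to 0.060 + 0.017 = 7.7%, while sharing among tested patients falls from 30% to 21%.

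The cost is a few lines of analysis and reporting text using data already in hand. The price is a weaker claim: this trial cannot give a randomised estimate of the app's effect on shared decision-making as this scale measures it.

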#### Preliminary Efficacy

An intent-to-treat analysis of all enrolled patients will be conducted according to random assignment of the intervention to estimate the effect of STIckER on STI testing. We will conduct a mixed-effects generalized linear model (GLM) with the logit link function to look at the effect of STIckER on STI testing, if there is a clustering effect by provider, or logistic regression if there is no provider effect. To determine whether there is a provider effect, we will assess the intraclass correlation coefficient (ICC) for the primary outcome using a null (empty) mixed-effects model with provider as a random effect. If the ICC is greater than 0.01, we will proceed with mixed-effects modeling; otherwise, we will use standard logistic regression. For other dichotomous outcomes, we will use the same analytic approach (GLM) with the logit link function if there is a provider effect or logistic regression if there is no provider effect.

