#### Secondary Efficacy and Implementation Outcomes

If there is a provider-level effect, we will use mixed-effect GLM to look at the association of STIckER on the continuous outcomes, such as implementation scales, and linear or logistic regression if there is no provider effect. If needed, we will also conduct sensitivity analyses to explore the effect of spillover, misclassification, missing data, or any other deviation from the study procedures that would affect efficacy or implementation outcomes.

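### Shared decision-making is a secondary efficacy outcome, but its scale is asked only when a test was ordered, so a between-arm comparison is not protected by randomisation

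*Protocol article*

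**What the plan says.** Secondary Outcomes in the protocol article names, as efficacy outcomes, "overall and site-specific STI positivity rate, decisional conflict, and level of shared decision-making". The only instrument the article gives for the last of these is the Control Preferences Scale.

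The Exit Survey section gives that scale to patients on a condition, written out for each arm: "if STI testing was ordered, then what level of shared decision-making involvement occurred using the control preferences scale". HCP-P Study Assessments puts the same condition on providers: "if STI testing was ordered what level of shared decision-making involvement occurred using the Control Preferences Scale". The intervention-arm providers get the same questions.

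The primary outcome is "the difference in the proportion of sexually active adolescents and young adults tested for Neisseria gonorrhoeae or chlamydia trachomatis between the 2 arms", and the Hypothesis section states the expected direction: "We anticipate that the intervention will lead to a higher proportion of adolescents and young adults receiving comprehensive genitourinary and extragenital STI testing".

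In the app itself, "Participants are taken through each recommendation with additional education and the option to opt in or opt out of testing".

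On analysis, Preliminary Efficacy says "An intent-to-treat analysis of all enrolled patients will be conducted according to random assignment"; that sentence is written for STI testing. For secondary outcomes, if there is a provider effect, "we will use mixed-effect GLM to look at the association of STIckER on the continuous outcomes, such as implementation scales". Neither section mentions that the scale is missing by design for patients without an order.

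**The concern.** A score exists only for patients in whom a test was ordered. Ordering follows randomisation and is the behaviour the app is built to change. If the app works, the intervention arm's respondents will include patients who would have had no order, and so no score, under usual care. Comparing the two groups of respondents compares different kinds of patient, even if the app changed nobody's experience of the decision.

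The condition also removes part of what the scale is meant to capture. The Exit Survey section describes it as measuring how far the decision about testing was shared. A considered decision not to test is such a decision, and the app offers that choice, but it is never scored.

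Shared decision-making is the mechanism the app is named for, and the pilot is meant to inform a multisite trial. A misleading contrast on this outcome would carry forward.

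**Working it through.** **1. The plan's own design figure.** The Power Analysis gives a minimum detectable effect of 0.348. With 44 providers, 140 patients, ICC 0.01 and 50% of variance explained at each level:

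(t.975,42 + t.80,42) × √[0.01×0.5/(0.25×44) + 0.99×0.5/(0.25×140)] = 2.868 × √(0.000455 + 0.014143) = 0.347.

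The figure is reproduced. The point does not depend on it; it only gives a scale for the results below.

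**2. Who has a score.**

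| Exit-survey item (patients) | Asked of |
|---|---|
| Testing discussed | everyone, both arms |
| Decisional conflict, 9 items | everyone, both arms |
| Control Preferences Scale | only if a test was ordered, both arms |

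An intent-to-treat comparison of all enrolled patients is possible for the first two rows and impossible for the third.

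**3. Size of the selection effect when the app has no effect on sharing.** The documents give no ordering rates and no relation between sharing and ordering, so both are assumed here. Let the sharing score be standard normal, with correlation ρ to a latent tendency to have a test ordered, and let a proportion p have an order. The mean score among those with an order is ρλ(p), where λ(p) = φ(z)/p and z is the upper-p normal quantile. The spurious difference (app minus control) is ρ₁λ(p₁) − ρ₀λ(p₀).

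λ(0.20) = 1.400, λ(0.30) = 1.159, λ(0.35) = 1.058, λ(0.40) = 0.966, λ(0.50) = 0.798, λ(0.54) = 0.735, λ(0.65) = 0.570.

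Two pairs correspond to two readings of the 35% in the Power Analysis: 0.40×1.35 = 0.54 and 0.30+0.35 = 0.65. Respondents are out of about 140/2 = 70 per arm. Entries are in SD.

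| Ordered, control v app | Respondents | ρ = ±0.3 both arms | ρ = ±0.5 both arms | ρ 0 v 0.3 | ρ −0.3 v 0.3 | ρ 0 v 0.5 |
|---|---|---|---|---|---|---|
| 20% v 35% | 14 v 24 | ∓0.10 | ∓0.17 | 0.32 | 0.74 | 0.53 |
| 30% v 50% | 21 v 35 | ∓0.11 | ∓0.18 | 0.24 | 0.59 | 0.40 |
| 30% v 65% | 21 v 46 | ∓0.18 | ∓0.30 | 0.17 | 0.52 | 0.28 |
| 40% v 54% | 28 v 38 | ∓0.07 | ∓0.12 | 0.22 | 0.51 | 0.37 |

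Simulation with 2,000,000 draws per scenario agrees with the formula for every scenario simulated. With ρ = 0 in both arms the difference is 0. With the same ρ in both arms, its sign is the opposite of the sign of ρ.

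**4. The same point in percentages.** Assume 30% have an order regardless of arm, 40% of them with a shared decision; the app adds a further 20% with an order; nobody's score changes. The proportion with a shared decision among the added patients is unknown:

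| Shared, among added patients | Among those with an order, control v app | Ordered and shared, per enrolled, control v app |
|---|---|---|
| 10% | 40% v (0.12+0.02)/0.50 = 28% | 12% v 14% |
| 40% | 40% v (0.12+0.08)/0.50 = 40% | 12% v 20% |
| 70% | 40% v (0.12+0.14)/0.50 = 52% | 12% v 26% |

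The conditional contrast runs from −12 to +12 points. The composite in the last column rises in every row, because testing rises.

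**5. Precision.** At 21 v 35 respondents and 40% v 52%, the standard error is √(0.40×0.60/21 + 0.52×0.48/35) = 0.136, about 14 points.

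**The case against.** The strongest reply has four parts.

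- **Nothing is shown to be biased.** The documents give no ordering rate and no link between sharing and ordering. The artefact can be zero, and a 12-point artefact would be smaller than its standard error of about 14 points. This stands as a limit on what can be claimed about size and direction. It does not restore comparability: the app acts on both ordering and sharing, so no relation between them would be a surprising default.
- **Comparative information on decisions is not lost.** Whether testing was discussed, the information items and decisional conflict are asked of everyone, and decisional conflict is itself a secondary efficacy outcome. This stands, and it shapes the fix. Decisional conflict does not measure who made the decision, however, so it is not a replacement for the scale.
- **Analysis detail belongs in the full protocol or analysis plan.** That is true of models and estimands. The collection rule is stated in the article itself, and no analysis plan can recover answers that were never requested. The sensitivity analyses for missing data, to be done if needed, do not obviously reach scores that are absent by design.
- **The condition is not the primary outcome.** It is a survey report that STI testing was ordered, not record-confirmed gonorrhoea or chlamydia testing. This is correct; the two events are close, not identical.

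A reader might infer that the STI positivity rate has the same fault. Secondary Outcomes states no denominator for it, so the documents do not support calling it an error.

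**Conclusion.** The point holds. The scale is observed only after a post-randomisation event that the app is expected to make more frequent, so a between-arm comparison of it is not protected by randomisation and should be expected to be biased. That the outcome is meant to be compared between arms is a fair reading of a secondary efficacy outcome measured identically in both arms, although the article does not say so in those words.

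Under the assumed rates and correlations, the spurious difference is about 0.07 to 0.30 SD in either direction with the same selection in both arms, and about 0.17 to 0.74 SD when selection differs by arm. Some of the latter exceed the plan's own 0.348. Only about 20% to 40% of control and 35% to 65% of intervention patients would contribute.

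Two stronger readings are tempting. One is that the comparison favours the app by a known amount; the sign and size rest entirely on inputs the documents do not give. The other is that an all-enrolled composite of test ordered and decision shared repairs the outcome. With no change in any score it still moves from 12% to between 14% and 26%, so it largely repeats the primary outcome, and it counts a shared decision not to test as a failure.

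**What to change.** 1. Report the Control Preferences Scale, from patients and from providers, descriptively among visits with a test ordered. Give the number and proportion responding in each arm, and state that this is not a randomised comparison. Draw no between-arm efficacy inference and give no p-value.
2. For comparative evidence on decision quality over all enrolled patients, use the items asked unconditionally: whether testing was discussed, and decisional conflict. These keep whatever protection the provider randomisation gives.
3. If a composite of test ordered and decision shared is wanted, add it as supplementary, define what counts as shared (the article gives a 1 to 5 scale and no cut-point), show its components, and do not label it an effect on shared decision-making.
4. In the multisite trial, ask the scale of every patient, worded so that a decision not to test can be scored.

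Items 1 to 3 cost only wording in the analysis plan and the results report. Enrolment and follow-up are complete, so scores for patients without an order cannot be recovered in this pilot. Item 4 adds one survey question for patients who currently skip it.
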